## Abstract

**Background:**

Post‐cardiac arrest care for patients resuscitated from out‐of‐hospital cardiac arrest (OHCA) includes multiple pharmacological and physiological interventions, yet optimal strategies to reduce post‐cardiac arrest syndrome–related morbidity and mortality remain uncertain. The DANOHCA (Danish Out‐of‐Hospital Cardiac Arrest) trial evaluates four such interventions—high‐dose dexamethasone, prophylactic olanzapine, elevated backrest position, and early wakeup—in a factorial trial framework. This manuscript presents the complete statistical analysis plan for analyses common to all four DANOHCA interventions.

**Methods:**

DANOHCA is an investigator‐initiated, multicenter, randomized, 2 × 2 × 2 × 2 factorial clinical trial enrolling comatose adult OHCA patients with a presumed cardiac etiology who achieve sustained return of spontaneous circulation, with randomization within 180 min of return of spontaneous circulation. Participants are co‐randomized to Dexamethasone versus placebo, olanzapine versus placebo, backrest elevation at 35° versus 5°, and early (≤ 6 h) versus late (28–36 h) wakeup, with pharmacological interventions blinded and physiological interventions open‐label. This statistical analysis plan specifies the primary and secondary outcomes, covariate adjustment, handling of missing data, assessments of interactions between interventions, and assumption checks, with all primary analyses conducted according to the intention‐to‐treat principle. The analysis plan is finalized prior to completion of randomization.

**Results:**

The primary outcomes are 90‐day all‐cause mortality for the dexamethasone and backrest interventions, and days alive outside hospital within 30 days for the olanzapine and early wakeup interventions, with common secondary and tertiary endpoints including mortality at later time points, neurological function, health‐related quality of life, organ function, and safety outcomes. Mixed‐effects regression models, Cox regression, stratified nonparametric tests, and prespecified sensitivity analyses will be applied to minimize bias and quantify intervention effects, including their associated uncertainties.

**Conclusion:**

This predefined statistical analysis plan provides a detailed, transparent framework for the primary analyses and reporting of the DANOHCA trial.

**Trial Registration:** Clinical Trials Information System (CTIS): 2024‐515997‐28‐00

## Background

1

Critical care management after out‐of‐hospital cardiac arrest (OHCA) aims to limit ischemia–reperfusion injury by targeting sedation, hemodynamics, ventilation, and temperature, but optimal strategies to reduce post‐cardiac arrest syndrome‐related morbidity and mortality remain uncertain [1, 2]. Post‐cardiac arrest syndrome comprises a systemic inflammatory response, cerebral and myocardial dysfunction, and the underlying precipitating pathology [3]. It results in high mortality rates and long‐term neurological disability despite contemporary intensive care, including temperature control and organ support. Several potentially modifiable treatment domains in the early post‐resuscitation phase—systemic inflammation, cerebral perfusion and intracranial pressure, duration of sedation, and delirium—are supported by expert consensus based on pathophysiological rationales and observational data but have not been evaluated in large, pragmatic, randomized trials in comatose patients resuscitated from OHCA.

The DANOHCA (Danish Out‐of‐Hospital Cardiac Arrest) trial is an investigator‐initiated, randomized, controlled, multicenter, 2 × 2 × 2 × 2 factorial clinical trial evaluating four distinct interventions in patients who remain comatose after resuscitation from OHCA.

The trial evaluates two pharmacological interventions, that is, high‐dose dexamethasone to control systemic inflammation and prophylactic olanzapine to prevent delirium, and two physiological interventions, that is, elevated backrest positioning to improve cerebral perfusion pressure and early versus late wakeup call to reduce exposure to deep sedation and facilitate earlier hospital discharge. In general intensive care, current guidelines advocate minimal sedation and daily wakeup calls [4]. However, in post‐cardiac arrest care, prolonged deep sedation for 24–48 h has been standard of care since the introduction of targeted temperature management, despite limited evidence [2, 5, 6]. The early wakeup intervention tests whether the principle of minimal sedation also applies after cardiac arrest.

These four interventions target distinct but complementary mechanisms in early post‐resuscitation care, systemic inflammation, delirium, cerebral perfusion, and sedation strategy, aiming collectively to reduce morbidity and mortality after cardiac arrest.

All patients are randomized in a 1:1 factorial design to all four interventions simultaneously.

The four hypotheses are:
*There is no difference in 90‐day all‐cause mortality between the dexamethasone and placebo groups*.

*Treatment with dexamethasone leads to improved rates of survival at 90 days compared to placebo*.

*There is no difference in 90‐day all‐cause mortality between backrest elevation at 35° and 5°*.

*An elevated backrest at 35° leads to improved rates of survival at 90 days compared to elevation at 5°*.

*There is no difference in days alive outside of hospital within 30 days between early wakeup (sedation ≤ 6 h) and mandatory sedation (28–36 h)*.

*Mandatory sedation for 28–36 h leads to more days alive outside of the hospital in 30 days compared to sedation for ≤ 6 h*.

*There is no difference in days alive outside of hospital within 30 days between Olanzapine and placebo*.

*Treatment with olanzapine leads to more days alive outside of the hospital in 30 days compared to placebo*.

This statistical analysis plan is one of several companion manuscripts for the DANOHCA trial, each addressing a prespecified intervention within the shared factorial trial framework. Intervention‐specific rationale and procedures are described in four corresponding protocol manuscripts; the present SAP outlines the methodological approach to analyzing the common primary, secondary, and tertiary outcomes of the DANOHCA trial. This predefined plan aims to minimize analytic bias, ensure transparency, and enhance the interpretability of intervention effects on clinically important outcomes.

## Methods

2

The DANOHCA trial is registered with the Clinical Trials Information System (CTIS) under trial number 2024‐515997‐28‐00. The design and interventions of the DANOHCA trial are described in detail in four dedicated protocol papers. Patients and members of the public were not involved in trial design, given the emergency circumstances of out‐of‐hospital cardiac arrest and patients' inability to participate in planning. The primary and secondary outcomes were selected to reflect priorities relevant to patients and their families, including survival and time alive outside the hospital.

In summary, the trial will enroll adults (≥ 18 years) admitted after OHCA with return of spontaneous circulation (ROSC). Patients will be eligible if they fulfill all predefined inclusion criteria and none of the exclusion criteria.

### Inclusion Criteria

2.1

Out‐of‐hospital cardiac arrest of presumed cardiac cause.Age ≥ 18 years.Sustained ROSC (defined as ≥ 20 min without chest compressions or mechanical circulatory support).Unconsciousness (Glasgow Coma Scale < 9, unable to obey verbal commands) upon admission.

### Exclusion Criteria

2.2

Presumed noncardiac cause of arrest.Unwitnessed asystole.Suspected or confirmed intracranial bleeding or stroke.Pregnancy.Admission temperature < 30°C.Persistent cardiogenic shock (systolic blood pressure < 80 mmHg despite fluid loading and vasopressor or inotropic medication).Known disease making 180‐day survival unlikely.Known pre‐arrest Cerebral Performance Category 3 or 4.> 180 min from ROSC to randomization.

### Randomization and Blinding

2.3

Randomization is performed in a 1:1 factorial design for all four interventions, using sealed intervention boxes containing study drugs and written instructions. Randomization is generated with varying block sizes to ensure balance across the 16 possible intervention combinations. The balance of allocation across the 16 possible combinations is monitored when generating the randomization sequence and as part of the planned interim analyses.

Pharmacologic interventions (dexamethasone and olanzapine) are double‐blinded, with study drugs prepared by the pharmacy in the Capital Region of Denmark and administered by nurses uninvolved in the patient's care. Physiologic interventions (backrest elevation and early wakeup) are open‐label because blinding them is inherently difficult. Outcome assessors, statisticians, data managers, the steering group, and the data safety and monitoring committee will be blinded to treatment allocation.

### Interventions

2.4

#### The Dexamethasone Intervention

2.4.1

Patients randomized to Dexamethasone receive 20 mg intravenously (administered as Dexamethasone phosphate) over 15 min as soon as possible after admission, followed by 20 mg intravenously daily at 0600 h (or at least 8 h after the initial dose) for two additional days, for a total of three doses. Patients in the control group receive a matching placebo (sodium chloride).

#### The Olanzapine Intervention

2.4.2

Patients randomized to olanzapine receive 10 mg via nasogastric tube as soon as possible after admission, followed by 10 mg daily at 6 PM (with a minimum of 12 h between doses) for two additional evenings, for a total of three doses or until intensive care unit discharge, whichever occurs first. Patients in the control group receive a matching placebo. All patients are monitored with mandatory telemetry for 96 h or until withdrawal of life‐sustaining therapies to assess for QT prolongation and arrhythmias.

#### The Backrest Elevation Intervention

2.4.3

Patients are randomized to either backrest elevation to 35° in the semi‐Fowler position (with the lower limb elevated) or backrest elevation to 5° during the initial 72 h or until extubation, whichever occurs first. Adherence to the assigned position is assessed every 8 h. The intervention could be temporarily discontinued for procedures or mobilization, but resume if invasive ventilation continues.

#### Early Wakeup Intervention

2.4.4

Patients are randomized to an early wakeup call after ≤ 6 h or a late wakeup call between 28 and 36 h after intensive care unit admission. Criteria for extubation readiness include Glasgow Coma Scale ≥ 12, Richmond Agitation‐Sedation Scale 0 to −1, ability to raise arm or voluntary handshake on command, successful spontaneous breathing trial, and low ventilator settings (pressure support ≤ 14 cm H_2_0 (or lower according to local practice), positive end‐expiratory pressure ≤ 8 cm H_2_O [10 cm H_2_O if obese], and fraction of inspired oxygen ≤ 40%). A wakeup call can be aborted in case of seizures, respiratory distress, shock, or other clinical reasons. Sedatives before the scheduled wake‐up call are permitted as needed for clinical care in the early‐wake‐up call group and are mandatory in the late wake‐up call group.

### Outcomes

2.5

#### Primary Outcomes

2.5.1

The trial employs intervention‐specific primary outcomes:
Dexamethasone intervention: All‐cause mortality at 90 days.Backrest elevation intervention: All‐cause mortality at 90 days.Olanzapine intervention: Days alive outside hospital within 30 days.Early wakeup intervention: Days alive outside the hospital within 30 days.

The choice of intervention‐specific primary outcomes reflects the anticipated mechanism of action for each intervention. Dexamethasone and backrest elevation target pathophysiological pathways that may directly affect early survival—dampening systemic inflammation and increasing cerebral perfusion pressure, respectively—thereby making 90‐day all‐cause mortality the most clinically relevant primary endpoint. In contrast, olanzapine and the early wakeup strategy primarily aim to reduce delirium and sedation‐related complications, translating into improved functional recovery and shorter hospital stays rather than a direct effect on mortality. Days alive outside the hospital within 30 days reflect both survival and time to recovery, and are therefore a more sensitive and clinically meaningful primary endpoint for these two interventions.

Days alive outside the hospital within 30 days are calculated by subtracting the time spent in the hospital or deceased within 30 days, then rounding down to the nearest whole number. Thus, a patient dying on admission day has zero days alive outside the hospital, and a patient with hospitalization exceeding 30 days also has zero days alive outside the hospital. A day (≥ 24 h) spent at a hospital or healthcare facility operated by a Danish region counts as time in hospital, whereas outpatient visits and brief hospitalizations < 24 h count as days alive outside hospital.

#### Secondary Outcomes

2.5.2

The following secondary outcomes are assessed across all four interventions. Intervention‐specific secondary outcomes are detailed in the four dedicated protocol publications.

Common secondary outcomes for all four interventions include:
All‐cause mortality at 90 days (for interventions where this is not the primary outcome).Days alive outside hospital within 30 days (for interventions where this is not the primary outcome).Cerebral Performance Category and modified Rankin Scale at follow‐up 3–6 months after cardiac arrest.

#### Exploratory (Tertiary) Outcomes

2.5.3

All‐cause mortality at 180 days and 1 year.Inflammatory and organ markers during the initial 72 h.Neurofilament light chain and neuron‐specific enolase at 0, 24, 48, and 72 h.Cognitive function assessment (Repeatable Battery for the Assessment of Neuropsychological Status, Trail Making Test, and Montreal Cognitive Assessment) at 3–6 months.

### Sample Size

2.6

The trial aims to include 1000 patients across five sites, covering the entire Danish population. Sample size calculations were performed separately for each intervention based on its primary outcome.

For the Dexamethasone and backrest elevation interventions (primary outcome: 90‐day mortality), assuming an overall mortality of 35% and a 25% relative risk reduction (to 26% mortality), with 85% power and a two‐sided significance level of 5%, 468 patients per group are required. To account for potential dropouts and loss to follow‐up, 500 patients per group (1000 total) are planned.

For the olanzapine and early wakeup interventions (primary outcome: days alive outside hospital within 30 days), estimates assumed 35% mortality during initial hospitalization (0 days alive outside hospital) and a mean of 15 days outside hospital for survivors, yielding a population mean of 9.8 days with an estimated standard deviation of 7 days. To detect an increase of 1.5 hospital‐free days with > 90% power and a two‐sided significance level of 5%, a total of 920 patients were required.

The combined sample size of 1000 patients provides adequate power for all four primary outcomes within the factorial design. The trial is not powered to detect interactions between interventions; prespecified interaction analyses (Section 3.5) are exploratory and hypothesis‐generating.

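### The planning SD of 7 days for days alive outside hospital lies below the minimum of 7.15 that Section 2.6's own inputs allow, so the statement of 920 patients for > 90% power has no valid basis

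*SAP article*

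**What the plan says.** All the figures are in Section 2.6 (Sample Size) of the SAP article.

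- **Olanzapine and early wakeup.** The plan assumes 35% mortality during the first admission, scored as 0 days, and "a mean of 15 days outside hospital for survivors", "yielding a population mean of 9.8 days with an estimated standard deviation of 7 days". No SD among survivors and no source for the 7 are given.
- **Target.** "To detect an increase of 1.5 hospital‐free days with > 90% power" at a two-sided 5% level, "a total of 920 patients were required".
- **Dexamethasone and backrest.** The calculation rests on "assuming an overall mortality of 35% and a 25% relative risk reduction (to 26% mortality"), with 85% power and 468 per group, raised to 500 per group for dropout.
- **Conclusion.** "The combined sample size of 1000 patients provides adequate power for all four primary outcomes within the factorial design".

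Two other sections bear on this. Section 3.2.2 makes the Wilcoxon rank-sum test the primary analysis of days alive outside hospital. Section 2.5.1 expects olanzapine and early wakeup to work through faster recovery and shorter stays, not through mortality.

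**The concern.** The mean of 9.8 is derived from a two-part population: a block of deaths at zero and a group of survivors averaging 15 days. The distance between those two parts already contributes a fixed amount of variance, and that amount alone exceeds 7 squared. The stated SD therefore leaves less than no room for variation among survivors, on a scale that runs from 0 to 30 days.

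Two of the four primary comparisons take their sample size from this SD. The figure of 920 also comes from a comparison of means, while the planned test ranks patients, with at least 35% of them tied at zero. If olanzapine or early wakeup turns out neutral, readers will judge the result against a stated power above 90% for 1.5 days. The inputs printed in the plan do not support that figure.

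**Working it through.** **1. Reproduce the plan's figure.** Inputs from Section 2.6: difference 1.5 days, SD 7, two-sided 5%, 90% power. Allocation is 1:1 (Section 2.3).

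n per arm = 2 × 7² × (1.960 + 1.2816)² / 1.5² = 457.7, so 458 per arm and 916 in total. Power is 90.1% at 920 and 92.3% at 1000. The 920 therefore reproduces with SD 7. The largest SD that keeps 90% power at 920 is 7.02.

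**2. The minimum SD under the stated inputs.** With a share 0.35 at 0 and a share 0.65 with mean 15 and SD s:

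- Mean = 0.65 × 15 = 9.75, which agrees with the stated 9.8.
- Variance = 0.35 × 0.65 × 15² + 0.65 × s² = 51.19 + 0.65 s².
- With s = 0, SD = √51.19 = 7.15. The stated SD of 7 means a variance of 49.

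Rounding of the inputs does not remove the conflict while the mean still rounds to 9.8. With 34.5% mortality and a mean of 9.75, the survivor mean is 9.75/0.655 = 14.89, and the minimum SD is 14.89 × √(0.345 × 0.655) = 7.08.

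**3. Power for 1.5 days.** The survivor SD s is an assumption in every row. The mean-based columns use the SD from step 2. The last column is simulated for the planned test with 500 per arm, survivors drawn from a beta distribution scaled to 0–30 days, 35% zeros in both arms, and the whole effect in survivors (a shift of 1.5/0.65 = 2.31 days).

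| Survivor SD | Population SD | Means, N = 920 | Means, N = 1000 | N for 90% (means) | Wilcoxon, N = 1000 |
|---|---|---|---|---|---|
| 0 | 7.15 | 88.9% | 91.2% | 958 | not simulated |
| 2 | 7.33 | 87.3% | 89.9% | 1006 | about 100% |
| 4 | 7.85 | 82.6% | 85.6% | 1152 | about 97% |
| 5 | 8.21 | 79.1% | 82.3% | 1260 | about 85% |
| 7 | 9.11 | 70.4% | 74.0% | 1552 | about 61% |
| 9 | 10.19 | 60.7% | 64.3% | 1940 | about 46% |

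The Wilcoxon figures move by a few points with the simulation run and with how days are rounded (87%, 58% and 44% at survivor SDs of 5, 7 and 9 in another run).

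For means at N = 1000, the largest SD that keeps 90% power is 7.32. That corresponds to s = √((7.32² − 51.19)/0.65), about 1.9 days.

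**4. Mortality figures.** The usual two-proportion formula with pooled variance under the null, 85% power and two-sided 5%, gives 468.4 per group for 35% against 26.0%. A 25% reduction from 35% is 0.75 × 35% = 26.25%, which needs 496.7, so 497 per group. The dropout margin within 500 is then 500 − 497 = 3 per group, not 500 − 468 = 32. Power at 500 per group for 26.25% is 85.2%.

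**The case against.** The strongest reply is that the error is small where it is certain. Moving from 7 to 7.15 costs about one point, and the trial recruits 1000 patients, not 920. At the minimum SD those 1000 patients still give 91.2%. Everything below 90% at 1000 depends on a survivor SD that the document does not contain. This stands. A reader might infer that the trial as planned fails to deliver > 90% power, and the document does not establish that.

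A second reply is that mean-based figures do not describe the planned test. This also stands. A reader might take 64–82% as the true power at 1000, but that range belongs to a comparison of means. Under a shift in survivors, the Wilcoxon test does better than that range when survivors are closely grouped and worse when they are widely spread.

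A third reply is that 7 could be an SD averaged over the two arms. If the 1.5 days came wholly from mortality (35% to 25%), the minimum averaged over arms would be 6.83, below 7. However, the plan attaches the 7 to the population with mean 9.8, and Section 2.5.1 does not expect a mortality effect. If the gain falls in survivors (mean 17.3), the arm-averaged minimum rises to 7.72.

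Finally, Section 3.2.2 requires confidence intervals, so a neutral result can be read from its interval. That limits the harm but leaves the stated planning figures wrong. The caveat in Section 4.2 concerns smaller true effects and does not address the SD.

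**Conclusion.** The contradiction is certain and needs no outside input: an SD of 7 cannot occur with 35% at zero and a survivor mean of 15. The 920 for > 90% power depends on that SD and is missed even in the most favourable case, though only by about one point.

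The practical size is conditional. It is nil at 1000 patients if survivors hardly vary. It becomes material if the survivor SD is around 5 days or more, which is plausible on a 0–30 scale but is an assumption here. The Wilcoxon figures also assume scaled-beta survivors and no mortality effect. What can be said is that the claim of adequate power for these two outcomes is unsupported as written, not that it is false.

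The mortality discrepancy is minor. A reader might infer that those two comparisons are underpowered, but 500 per group still gives about 85% at 26.25%, and Section 3.6 expects little missing primary outcome data. Only the stated dropout margin is affected.

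**What to change.** Keep 1000 patients and revise Section 2.6:

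1. State the SD among survivors, with its source, and derive the population SD as √(51.19 + 0.65 s²).
2. Replace the statement of 920 patients for > 90% power with simulated power of the Wilcoxon test for 1.5 days at N = 1000, over a range of survivor SDs. State whether the effect is placed in survivors, in mortality or in both.
3. Qualify the sentence on adequate power for all four primary outcomes to match those results.
4. Minor: reconcile the relative reduction with the target mortality. Either keep 26.0% and 468 per group and describe the reduction as 25.7% (9/35), or keep 25% and write 26.25% with 497 per group and a dropout margin of about 3.

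The cost is a short simulation and changed wording. No patients, tests, analysis sets or decision rules change. The stated power may become less favourable, depending on the survivor SD that the sponsor can support.

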## Statistical Analysis Principles

3

### General Principles

3.1

All analyses will be conducted according to the modified intention‐to‐treat principle, including all randomized participants who meet the inclusion criteria and have available outcome data, or imputed outcome data (see missing data section below). Participants who do not fulfill the inclusion criteria will be excluded from analyses. If consent is subsequently withdrawn, data collected prior to withdrawal will be included in the primary analysis in accordance with the EU Clinical Trials Regulations, unless the participant explicitly requests deletion of their data. A per‐protocol analysis will be performed as a sensitivity analysis, including only participants who received all scheduled doses of pharmacologic interventions, adhered to the assigned backrest position for ≥ 80% of the time, and had a wakeup call attempted within the assigned time frames.

Data will be analyzed and reported as four individual trials, with no adjustment for multiple comparisons planned. This approach is justified because almost all previous trials in the hospital phase of out‐of‐hospital cardiac arrest care have been neutral, and all four interventions are accepted without considering potential interactions. If more than one intervention shows a non‐neutral result, interactions between interventions will be evaluated by including pairwise and higher‐order interaction terms in the primary regression models for each intervention, applying the prespecified thresholds defined in Section 3.5 (interaction *p* < 0.01 and absolute effect ≥ 5.6%). If a clinically important interaction is identified, results for the affected interventions will be presented both as overall estimates and stratified by the interacting intervention allocation. All regression analyses will be adjusted for site as a covariate.

All statistical significance tests will be two‐sided, with a significance level of 5%. No alpha spending or adjustment of the final significance level is required, as the planned interim analysis at 500 enrolled patients is a safety review conducted by the independent data‐monitoring committee without formal efficacy or futility testing (see Section 3.9). Throughout, categorical variables will be presented as counts with proportions, whereas continuous variables will be presented as means ± standard deviations for normally distributed variables or medians (25th–75th percentiles) for nonnormally distributed variables. The normal distribution will be evaluated using quantile‐quantile plots.

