### Methodologic Considerations

4.4

The factorial design requires careful attention to potential interactions. If interventions act through independent mechanisms without synergy or antagonism, factorial analysis is efficient and valid. However, if substantial interactions exist, main effects may be misleading. This plan includes rigorous assessment of interactions, with criteria for both statistical significance (*p* < 0.01) and clinical importance (absolute effect ≥ 5.6%) to avoid false‐positive findings. If important interactions are identified, results will be presented with appropriate stratification.

The modified intention‐to‐treat approach balances statistical rigor with clinical pragmatism. Including only participants who meet the inclusion criteria avoids diluting treatment effects from ineligible patients while maintaining randomization integrity. Per‐protocol analyses will provide complementary information about intervention effects under ideal adherence but must be interpreted cautiously given potential selection bias.

Handling of missing data follows current best practices. Registry linkage for mortality ensures complete ascertainment of the primary outcome for Dexamethasone and backrest interventions. Days alive outside the hospital can be ascertained from hospital records and national registries with minimal missingness. Nevertheless, the plan includes multiple imputation and sensitivity analyses to assess the robustness of the findings under different missing‐data assumptions.

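### The abstract promises intention-to-treat for all primary analyses, but Section 3.1 drops randomised patients judged not to meet the inclusion criteria, without safeguards and with no all-randomised analysis planned

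*SAP article*

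**What the plan says.** **Primary population.** The abstract's Methods paragraph describes the plan as one "with all primary analyses conducted according to the intention‐to‐treat principle". Section 3.1 says otherwise: "All analyses will be conducted according to the modified intention‐to‐treat principle", followed by "Participants who do not fulfill the inclusion criteria will be excluded from analyses". Section 4.4 defends the modified set: "Including only participants who meet the inclusion criteria avoids diluting treatment effects from ineligible patients while maintaining randomization integrity".

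**Eligibility and blinding.** Section 2.1 lists four inclusion criteria: presumed cardiac cause, age, sustained return of circulation, and unconsciousness on admission. Section 2.3 makes the two drugs double-blind and the backrest and wakeup interventions open-label. It lists outcome assessors, statisticians, data managers, the steering group and the monitoring committee as blinded. It does not say who decides after randomisation that a patient failed the inclusion criteria, when, or on what information.

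**Per-protocol set.** Section 3.1 adds a narrower population: "A per‐protocol analysis will be performed as a sensitivity analysis", "including only participants who received all scheduled doses of pharmacologic interventions", who also kept the backrest position for at least 80% of the time and "had a wakeup call attempted within the assigned time frames". The early window closes at 6 h; the other arm has "a late wakeup call between 28 and 36 h after intensive care unit admission" (Section 2.4.4). Section 4.2 warns of selection bias if nonadherence is related to prognosis and calls the results exploratory.

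**The concern.** The two definitions give different denominators for every primary result, and the analyst cannot follow both.

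The definition in Section 3.1 is also the weaker one. Removing randomised patients is harmless only if the decision uses facts fixed before randomisation and is made without knowledge of arm or course. Age and admission coma scale meet that test easily. Presumed cause of arrest is less secure, because imaging, laboratory results and the clinical course keep arriving after randomisation. Staff who know the backrest or wakeup allocation could then, without intending to, apply the label differently by arm. Because the modified rule covers all analyses, and the only other population is the narrower per-protocol set, a reader of the results could not test whether the exclusions mattered.

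The secondary concern is the per-protocol rule. It can require survival to a certain hour before a patient counts as adherent, and it does not say what happens to those who die first.

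**Working it through.** **1. The definitions side by side.**

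| Place | Set | Scope |
|---|---|---|
| Abstract, Methods | intention-to-treat | all primary analyses |
| Section 3.1 | modified, inclusion-criteria failures removed | all analyses |
| Section 4.4 | modified, said to preserve randomisation | general |
| Section 3.1 | per-protocol | sensitivity analysis |

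No row after the first contains all randomised patients.

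**2. The plan's own sample sizes (Section 2.6).** Both reproduce.
- Mortality 35% vs 26%, 85% power, two-sided 5%: n = [1.960·√(2·0.305·0.695) + 1.036·√(0.35·0.65 + 0.26·0.74)]² / 0.09² = 468.4, against 468 per group stated.
- Days alive outside hospital, difference 1.5, SD 7, 90% power: n = 2·(1.960 + 1.282)²·7²/1.5² = 457.7, so 458 per group or 916 in total, against 920 stated.

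**3. Power with and without exclusion.** The SAP gives no exclusion rate; 5% is assumed. The last row further assumes that the 5% respond not at all, so the effects shrink to 0.95 × 0.09 = 0.0855 and 0.95 × 1.5 = 1.425 days.

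| Per group | Effect | Power, mortality | Power, days |
|---|---|---|---|
| 500 (all kept) | as planned | 87.2% | 92.3% |
| 475 (5% excluded) | as planned | 85.5% | 91.0% |
| 500 (all kept) | diluted by 5% | 83.5% | 89.6% |

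Compared with excluding these patients, keeping them therefore costs at most about 2 points of power in this example.

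**4. Per-protocol set: two readings of one sentence.**

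*Reading A: the wakeup criterion is applied alone, or death ends the dose schedule.* An early-arm patient qualifies by about 6 h; a late-arm patient must live until a call is attempted at 28 to 36 h. Inputs from the SAP: no true effect, 35% mortality in both arms, 15 days for survivors, SD 7, 500 per arm. Assumed, because the SAP gives no figure: 1% die before the early call and a further x before the late call.
- Early-arm mortality: (0.35 − 0.01)/(1 − 0.01) = 34.3%.
- Late-arm mortality: (0.35 − 0.01 − x)/(1 − 0.01 − x).
- Spurious gain for the late arm: 15 × (early mortality − late mortality).
- Rejection rate: two-sided normal test of means at 5%, an approximation to the planned rank test.

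| x | Late-arm mortality | Spurious gain | Rejection rate (nominal 5%) |
|---|---|---|---|
| 2% | 33.0% | 0.20 days | 7% |
| 5% | 30.9% | 0.52 days | 21% |
| 8% | 28.6% | 0.87 days | 48% |

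*Reading B: all three doses are required of everyone.* Section 2.4.2 puts the second olanzapine or placebo dose at 6 PM, at least 12 h after the first, and the third an evening later, so the third falls at least 12 + 24 = 36 h after the first. A patient who dies before then fails in either wakeup arm, and the between-arm difference from this source is 0. Instead, early deaths are deleted from both arms of comparisons in which mortality is an outcome.

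**The case against.** **On the modified set.** All four inclusion criteria are admission facts, and a later non-cardiac diagnosis does not undo what was presumed at admission. Both drugs are double-blind, statisticians, data managers and the steering group are blinded, and Section 3.12 keeps allocation coded until the conclusions are accepted. Much of this stands. A reader might infer that all four primary results are equally exposed. The documents do not support that: knowledge of allocation can act directly only on the backrest and wakeup comparisons. What remains is that the SAP never says the exclusion is made by blinded people or from pre-randomisation information. The safeguards it lists do not name an eligibility assessor.

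**On the per-protocol set.** It is a labelled sensitivity analysis, its selection bias is disclosed in Sections 4.2 and 4.4, and it should not decide a primary conclusion. That also stands. A reader might infer that the rule deletes deaths between 6 and 36 h mainly from the late-wakeup arm. The text does not establish this: the criteria are joined by and, and under Reading B such deaths leave both arms. Even under Reading A, a late-arm death after 28 h is removed only if no call had yet been attempted. The direction is fixed only with perfect compliance, since early-arm patients with no attempt by 6 h would also drop out. The disclosed caveat does not settle the matter, however, because it concerns nonadherence and not compliant patients who die before an item falls due.

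**Conclusion.** The contradiction between the abstract and Sections 3.1 and 4.4 is established from the text alone and needs no assumption. The primary population must be stated once. As written, the exclusion of randomised patients is not protected against knowledge of arm or course, and the claim that randomisation is preserved is unsupported. The resulting bias cannot be sized, because the SAP gives neither an exclusion rate nor the outcomes of those excluded. The case rests on an open and avoidable route to bias, mainly for the two open-label interventions, and not on a demonstrated distortion.

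The per-protocol point is secondary and conditional. The rule is ambiguous about early deaths. The spurious 0.2 to 0.9 days, against a target of 1.5, arises only under Reading A and only with the assumed 2% to 8% dying between the calls. Under Reading B it is zero, and the defect is instead that survival past the dosing period is required in both arms.

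**What to change.** 1. In Section 3.1, define the primary set as all randomised patients with available or imputed outcome data, analysed as allocated, in line with the abstract. The existing provision for patients who ask for their data to be deleted can stay.
2. Move the eligibility-restricted set to a sensitivity analysis. State that eligibility is judged blind to allocation and outcome, from information recorded before randomisation only.
3. Correct Section 4.4 so that it no longer claims that the restriction in itself maintains randomisation.
4. Define the per-protocol set separately for each intervention. State how a patient who dies before a scheduled dose or wakeup window is classified, and apply the same survival requirement to both arms, for example a common landmark time. Counting a wakeup as due only while the patient is alive is not enough: it keeps late-arm deaths before 28 h but still drops early-arm patients who had no attempt by 6 h and died later.

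The cost is SAP wording, and the abstract says the plan is finalised before randomisation completes. The statistical downside is slight dilution from a few ineligible patients. A landmark also has a price: the per-protocol result then applies only to patients alive at that time, which should be stated.
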